### Study medication

For arms A, B and the control, medications will be funded by the PBS and dispensed utilising standard pharmacy practices. The type of DAAs used to treat participants with HCV in these arms will be at the discretion of the clinical service where the participant is enrolled. For arm C, study medications will be stored and dispensed by participating study sites. The medication used in arm C of this study is a 12 week course of oral combination therapy sofosbuvir/velpatasvir (Epclusa).

Epclusa tablets contain 400 mg of sofosbuvir and 100 mg of velpatasvir, to be taken orally once daily. Epclusa is TGA approved with ARTG ID 266823.^35^

### Assignment of interventions

Intervention arms will be assigned to sites using random number generation in a centralised system. Sites will be randomised in batches of six to ensure a balance of the number of sites in each arm over time. Sites will be informed of their allocation to each of the two consecutive arms separately. Due to the nature of the study design, it is not possible to blind clinics or participants during all phases of the intervention. All sites randomised to arms A, B or C in the first period will know that they will be allocated to the control arm after the cross-over period, due to the nature of the study design. Sites allocated to the control arm in the first period will be blinded as to which arm they will be randomised to, following the cross-over washout period (see figure 1).

### Study outcomes

The two primary outcomes of this trial include:

The proportion of participants commencing HCV treatment in each arm. Commencement of HCV treatment is defined as receipt of a script for treatment in arms A, B and control and as commencement of treatment with study drug in arm C. The proportion commencing treatment in each intervention arm will be compared with the control arm.The proportion of participants with HCV who start treatment achieving cure. Cure will be assessed by review of medical records for a clinic visit to assess SVR; if no visit has taken place, the study nurse will contact the participant to arrange one in all arms except the control.

Commencing treatment is an important and easily measurable outcome in clinical practice. The rationale for two primary outcomes is that arm C itself involves providing treatment to everyone found to have HCV as part of its intervention.

Secondary outcomes of this study include:

Time to treatment commencement is defined as number of days from first test to first dose of treatment.Case finding is defined as the proportion of people diagnosed with HCV among all those recruited.Cost-effectiveness is defined as the incremental cost to find and commence treatment among one person living with HCV from a health system perspective.

Participant acceptability is based on qualitative evaluation subject to further substudy design and ethical approval.

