**Methods and analysis:**

A cluster randomised cross-over trial will be conducted with three intervention arms and a control arm. Arm A will receive rapid hepatitis C virus (HCV) antibody testing; arm B will receive rapid HCV antibody and rapid RNA testing; arm C will receive rapid HCV antibody testing and same-day treatment initiation for HCV antibody-positive participants; the control arm will receive standard of care. The primary outcomes will be (a) the proportion of participants with HCV commencing treatment and (b) the proportion of participants with HCV achieving cure. Analyses will be conducted on an intention-to-treat basis with mixed-effects logistic regression models.

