#### Arm C: same-visit rapid POC antibody+treatment commencement

##### Baseline visit

Participants will receive an OraQuick rapid HCV antibody test using a fingerstick specimen, according to the manufacturer’s instructions, with the result documented at 20 min. The result from the 20 min time point will be provided to the participant as a preliminary result, with laboratory testing on a venous sample required to confirm. Blood samples will be collected for any confirmatory laboratory testing and SOC pretreatment screening.Participants with a negative OraQuick result will be advised that the POC test result will be confirmed by standard pathology results and they will be contacted in 1–2 weeks with these results.Participants with a positive OraQuick result will be provided with 2 weeks of sofosbuvir/velpatasvir (Epclusa) and will be instructed to begin treatment. In this sense, arm C uses presumptive treatment, where 14 days of treatment will be dispensed prior to laboratory confirmed diagnosis.^34^ Blood samples will be sent for confirmatory HCV antibody and RNA testing. Participants of childbearing potential will be screened for possible pregnancy and if indicated, a urinary pregnancy test will be performed before dispensing Epclusa. If the pregnancy test is positive, they will not be provided with a study drug and will be referred to SOC. Medical records will be reviewed for potential drug-drug interactions with Epclusa, and participants will be asked about medications they are currently taking. Participants taking medications with red or orange drug–drug interactions will not be provided with a study drug and will be referred to SOC.

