##### Weeks 1–2 (confirmatory results)

Participants will be contacted with the results of their confirmatory laboratory blood tests. Participants with a positive confirmatory antibody and negative RNA test result will be contacted with this result of prior exposure, no current infection and instructed to discontinue treatment and dispose of any unused medications. They will complete the study here. Standard harm minimisation messaging and window periods for detection of HCV will be discussed with the participant.Participants with a positive confirmatory antibody and positive confirmatory RNA result will be contacted to arrange ongoing treatment through the study, a further 4 weeks of sofosbuvir/velpatasvir will be dispensed. Further assessment may be required based on the laboratory blood test results:If the participant received an Aspartate Animotransferaese (AST):Platelet Ratio Index score of <1.0, they will be instructed to continue treatment as they were originally instructed.If the participant received an AST:Platelet Ratio Index score of ≥1.0, they will be instructed to continue taking the DAAs and will be referred to a specialised.Participants found to have renal impairment (estimated glomerular filtration rate (eGFR) <30 mL/min) or coinfected with chronic hepatitis B will be instructed to cease treatment and will be referred to a specialist.Participants found to have HIV infection will be instructed to continue the DAAs and be referred to a specialist.

Following specialist assessment, the participant may be required to change medications or alter their treatment course, according to the specialist’s recommendations.

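### As defined in Study outcomes, primary outcome 1 counts arm C drug starts in people without HCV; the abstract's definition of the same outcome does not

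*Protocol article*

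**What the plan says.** The Study outcomes section gives primary outcome 1 as "The proportion of participants commencing HCV treatment in each arm". The event is not the same everywhere: "Commencement of HCV treatment is defined as receipt of a script for treatment in arms A, B and control and as commencement of treatment with" (for arm C, study drug). It then says: "The proportion commencing treatment in each intervention arm will be compared with the control arm". The abstract describes the same outcome as "the proportion of participants with HCV commencing treatment".

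The arm C baseline visit reads: "Participants with a positive OraQuick result will be provided with 2 weeks of sofosbuvir/velpatasvir (Epclusa) and will be instructed to begin treatment" (subject to pregnancy and interaction checks). The protocol is open about the timing: "arm C uses presumptive treatment, where 14 days of treatment will be dispensed prior to laboratory confirmed diagnosis". At weeks 1–2, a participant with a positive confirmatory antibody and a "negative RNA test result will be contacted with this result of prior exposure, no current infection and instructed to discontinue treatment".

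In arms A and B, participants with a negative laboratory RNA result complete the study, and the week 12 prescription check is made in those with HCV.

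The reason given for having two primary outcomes is that "arm C itself involves providing treatment to everyone found to have HCV as part of its intervention".

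The Sample size and Statistical analysis sections name three main comparisons: A v control and B v control on uptake, and C v control on cure. C v A and C v B on uptake are also planned, as subgroup analyses.

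**The concern.** The article gives two populations for one primary outcome, and the choice matters mainly for arm C. Someone who has cleared the virus but remains antibody-positive can be handed study drug, take a dose, and only then learn that there is no infection. Under the Study outcomes wording that person has already met the event. The arm A and B pathways do not lead an RNA-negative participant to a script. The control arm follows usual clinic practice, which is taken here to reserve scripts for confirmed infection.

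The rationale sentence hides the problem, because it describes dispensing on antibody status as treatment of people found to have HCV.

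What is at stake is the reading of arm C's uptake result. The larger the share of antibody-positive recruits without infection, the better arm C looks, and exposure of uninfected people to drug is scored as success. This would remain even if script and first dose were made the same event in all arms, since it concerns who is counted rather than when.

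**Working it through.** **Plan figures used.** Alpha per comparison is 0.05/3 = 0.0167, as stated. The cluster-period size is 24; 24/0.8 = 30 and 30 sites × 2 periods × 40 = 2400 also reproduce. The control uptake rate of 30% and the site numbers (10 for arm A, 8 for arms B and C) come from the Sample size section.

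**Assumed, because the article does not give them.** Antibody-positive share of recruits (Ab), RNA-positive share of those (V), ICC and cluster autocorrelation (CAC).

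**Counted uptake per recruit, Study outcomes wording.** Let u be the uptake rate among infected people in control and s the arm C start rate among antibody-positive people.

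- Control: Ab × V × u
- Arm C: Ab × V × s + Ab × (1 − V) × s = Ab × s
- Spurious part: Ab × (1 − V) × s

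RNA status is unknown when arm C drug is dispensed, so the same s applies to infected and uninfected people. No effect on treating infected people therefore means s = u.

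**Central case: Ab = 0.5, V = 0.4, u = s = 0.30.**

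- Control: 0.5 × 0.4 × 0.30 = 0.06
- Arm C: 0.5 × 0.30 = 0.15
- Spurious part: 0.5 × 0.6 × 0.30 = 0.09, the whole difference

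**Range, Ab 0.3 to 0.7 and V 0.3 to 0.6.**

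- Smallest: 0.3 × 0.4 × 0.30 = 0.036 (5.4% v 9.0%)
- Largest: 0.7 × 0.7 × 0.30 = 0.147 (6.3% v 21.0%)

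**Chance that a test favours arm C when no more infected people are treated.** Cluster cross-over trials were simulated with 8 or 10 sites, 24 per site-period, and latent-scale ICC 0.02 with CAC 0.8 or ICC 0.10 with CAC 0.5. A t-test was applied to within-site differences at two-sided 0.0167, counting rejections in favour of arm C. The nominal rate in that direction is 0.0167/2, about 0.8%.

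- Central case: about 29% (8 sites, ICC 0.10) to about 62% (10 sites, ICC 0.02)
- Over the range above: about 6% to about 95%

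**Under the abstract's population.** RNA-negative starters are in neither numerator nor denominator. With s = u the difference is 0.

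**The case against.** **The abstract already excludes these people.** It limits the outcome to participants with HCV, and the arm A and B week 12 checks do the same. The planning rates point that way too: a 90% start rate per recruit in arm C would need at least 90% of recruits to be antibody-positive. This stands as evidence of what was probably meant. It does not remove the defect, because the section that defines the outcome says otherwise. That same section limits outcome 2 to participants with HCV, so the missing limit on outcome 1 cannot be read as house style.

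**The confirmatory result for arm C does not rest on uptake.** This stands in full. A reader might infer that the trial's main conclusion about arm C is biased. It is not: the 0.05/3 level is allocated to A and B v control on uptake and to C v control on cure. C v control on uptake is a stated comparison without allocated alpha, so 0.0167 serves above only as a yardstick.

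**The size can be overstated.** A reader might combine the planned 90% arm C start rate for uninfected people with 30% for infected people. At Ab = 0.5 and V = 0.4 that gives 6% v 33% and rejection in 97–100% of trials. The documents do not support that null: with RNA unknown at dispensing, nothing in the protocol would make acceptance differ threefold by RNA status. If 90% start, infected people start too. Arm C is then 0.5 × 0.9 = 45% against 6%; of the 39 points, 0.5 × 0.4 × (0.9 − 0.3) = 12 are real and 0.5 × 0.6 × 0.9 = 27 are spurious. The uptake effect is then inflated rather than invented.

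**The simulated test is not the planned model.** True. The plan is a mixed logistic model with pooled controls. The rejection rates are therefore indicative; the difference per recruit is plain arithmetic.

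**Conclusion.** The point holds in limited form. The abstract and the Study outcomes section give different populations for primary outcome 1. Under the latter, uninfected arm C starters count as commencing HCV treatment. That biases the stated comparison of arm C with control on uptake, and the C v A and C v B uptake analyses, in favour of arm C. None of the three main comparisons is affected.

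The spurious difference per recruit is the antibody-positive share times the RNA-negative share of those times the share who start drug. It is 9 points in the central case and 3.6 to 14.7 points over the range examined. These sizes rest on assumed prevalences and an equal 30% start rate; the rejection rates rest also on the assumed ICC and CAC. The direction does not depend on those values, provided that some antibody-positive recruits are RNA-negative and start drug, and that scripts in the other arms go only to people with confirmed infection. The wording should be corrected before the uptake results are analysed.

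**What to change.** 1. In Study outcomes, state one population for outcome 1, matching the abstract, by requiring laboratory-confirmed HCV RNA on the enrolment sample for the event in every arm. RNA-negative arm C starters are then never counted as commencing treatment.
2. Report RNA-negative arm C participants given study drug as a separate outcome: number, proportion and days of drug taken.
3. Correct the rationale sentence so that it describes arm C as providing treatment to everyone found to be HCV antibody-positive, in line with the arm C baseline visit.

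The cost is small. The first and third changes are to wording, and arm C already sends blood for confirmatory RNA testing. Days of drug taken may need a question at the weeks 1–2 contact if they are not already recorded. Arm C's uptake figure becomes less favourable. No dispensing or clinical rule changes.

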The QuickStart Trial will first determine the effectiveness of rapid POC testing in primary healthcare settings on treatment uptake. We hypothesise that rapid antibody testing alone (arm A), and rapid antibody followed by immediate RNA testing (arm B), will increase treatment uptake compared with standard clinical care (the control arm). Second, QuickStart will determine the effectiveness of POC antibody testing followed by same-day treatment (Arm C) on cure. We hypothesise that testing and same-day treatment will increase cure compared with standard clinical care. Our secondary outcomes will also compare each of the three intervention models to each other for any incremental benefit on treatment uptake and cure.

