### Sample size

Comparisons of primary interest are comparing outcome 1 (treatment commencement) in control and arm A; outcome 1 in control and arm B; and outcome 2 (HCV cure) in control and arm C. We consider sample size calculations with a minimum of 80% power and a significance level of 0.05/3=0.0167. Comparisons of control versus A are expected to result in the smallest required sample sizes so sample size calculations focus on this comparison. We use the Shiny CRT app^36^ for sample size calculations, assuming that the t- distribution is used instead of the normal approximation (accounting for small numbers of clusters).^37^

We suppose that five sites are assigned to each of the six treatment sequences. We found that with 24 participants recruited in each cluster in each period, power will be greater than 80% to detect a change in proportions of participants starting HCV treatment of 30%–50% where 10 clusters are allocated to arm A. Due to the greater portion of participants expected to start treatment in arm B (70%) and arm C (90%), power >80% is achieved with eight clusters assigned to the sequences that involve arms B or C (ie, with four clusters randomised to each of the arm B then control; control then arm B; Arm C then control; and control then arm C sequences). The proportion of participants expected to achieve cure in each arm are 10% among controls, 30% in arm A, 50% in arm B and 70% in arm C. Allowing for 20% loss to follow-up of sites and of participants, 30 participants per site per period would need to be recruited. Given these results, we will instruct sites to aim for 40 participants per site per period to counteract instances where some sites are unable to achieve 30 participants per site per period; some sites achieving 40 participants will balance sites which achieve <30. This would imply a maximum total of 2400 participants would need to be recruited.

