### Statistical analysis

Results from the trial will be reported according to the CONSORT extension statement for cluster randomised trials,^38^ or a CONSORT extension statement for cluster randomised crossover trials if one is available prior to end of data collection. Clinic and patient demographics will be described by site and study period. Analyses will be conducted on an intention-to-treat basis, with patients analysed according to the randomised treatment of their cluster at the time of their inclusion in the study. All available binary outcomes will be analysed at the patient level using mixed-effects logistic regression models with random intercepts for clinic and clinic period and fixed effects for interventions.^39^ ORs and 95% CIs will be reported; in addition, we will calculate and report risk differences and 95% CIs.

There are three main comparisons proposed, namely, treatment uptake outcome in arm A versus control (comparison 1) and arm B versus control (comparison 2) and HCV cure in Arm C versus control (comparison 3). Incremental benefits of arm B to arm A, and arm C to arm B, and arm C to arm A on treatment uptake and HCV cure will be performed in subgroup analyses. Data from controls in each arm will be pooled and a single model fitted for each outcome.

Randomisation will occur in batches of six, performed by the coordinating centre and concealed from investigators and sites until after site governance approcal. Since randomisation is occurring within batches of six services, fixed effects for batch will be included in these models. The Kenward-Roger correction will be applied to adjust for the small number of clinics.^40^ Estimates of intracluster correlations (within-period and between-period) will be reported. Time-to-event outcomes such as time to complete diagnosis will be analysed using Cox proportional hazards models with shared-frailty terms for site and fixed terms for treatment group and randomisation batch. There may be imbalances between sites with respect to various clinic and patient-level characteristics, and secondary analyses will adjust for these.

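### Treatment commencement is a script in arms A, B and control but a study-drug start in arm C, so the secondary uptake contrasts with arm C compare two different events

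*Protocol article*

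**What the plan says.** Study outcomes defines commencement of treatment, the first primary outcome, as "receipt of a script for treatment in arms A, B and control and as commencement of treatment with study drug in arm C". The next sentence there reads "The proportion commencing treatment in each intervention arm will be compared with the control arm", which takes in arm C.

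Two further uptake contrasts with arm C follow. The Introduction says the secondary outcomes will "compare each of the three intervention models to each other for any incremental benefit on treatment uptake and cure". Statistical analysis says that the comparisons of "arm C to arm B, and arm C to arm A on treatment uptake and HCV cure will be performed in subgroup analyses". The same section pools the controls and fits one model per outcome, and it analyses each participant under the arm the site was in when that participant joined.

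The comparisons of primary interest are narrower. Sample size lists A against control on uptake, then "outcome 1 in control and arm B; and outcome 2 (HCV cure) in control and arm C". Statistical analysis repeats these three.

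For arm C, the Baseline visit text says that participants with a positive pregnancy test or certain drug interactions "will not be provided with a study drug and will be referred to SOC".

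**The concern.** A script and a start are different facts, and the article treats them so. At week 12 in arms A and B, the nurse asks those who were given a prescription whether and when they began. The secondary time-to-commencement outcome runs to the first dose. In A, B and control the drug still has to come through a pharmacy; in arm C the site dispenses it.

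Two consequences follow for any uptake contrast involving arm C:

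- One side can count scripts that never led to treatment, while the other counts only treatment begun.
- The arm C rule is tied to study drug. A participant sent to standard of care stays in arm C for analysis, and a script obtained by that route does not meet the definition as written.

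The three contrasts would then estimate a difference in definition mixed with a difference in care. Because one model is fitted per outcome, both events enter the same regression as one variable.

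**Working it through.** **Step 1. Which contrasts are affected.**

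| Uptake contrast | Event on each side | Where planned | Status |
|---|---|---|---|
| A v control | script / script | Sample size, Statistical analysis | main; like for like |
| B v control | script / script | Sample size, Statistical analysis | main; like for like |
| C v control | study-drug start / script | Study outcomes | not a main comparison |
| C v A | study-drug start / script | Introduction, Statistical analysis | secondary |
| C v B | study-drug start / script | Introduction, Statistical analysis | secondary |

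The third main comparison, C against control, is on cure. The Sample size significance level of 0.05/3 = 0.0167 covers only the three main comparisons.

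**Step 2. The plan's own figures.** Sample size expects uptake of 30% (control), 50% (A), 70% (B) and 90% (C). The differences are C − control = 60 points, C − A = 40 and C − B = 20.

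**Step 3. Arm C participants on the standard-of-care route.** Let d be the share of arm C participants with HCV who are diverted, and s the share of those who then receive a script. Uptake left out of arm C is d × s. The article gives neither, so both are assumed: d from 0.05 to 0.15 and s from 0.30 to 0.50.

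- Lowest: 0.05 × 0.30 = 0.015, or 1.5 points.
- Highest: 0.15 × 0.50 = 0.075, or 7.5 points.

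**Step 4. Scripts that never lead to a start.** Let q be the share of scripts that lead to a start. The article does not give it; 0.80 to 1.00 is assumed. The result depends on what the planning rates mean.

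- If 70% in arm B is a script rate, C − B on a common start definition is 0.90 − 0.70q: 20 points at q = 1.00, 23.5 at 0.95, 27 at 0.90 and 34 at 0.80. Over the same range C − A (0.90 − 0.50q) runs from 40 to 50 points and C − control (0.90 − 0.30q) from 60 to 66.
- If 70% is already a start rate, as the Sample size wording suggests, the true start difference stays at 20 points. The difference as defined is then 0.90 − 0.70/q: 16.3 points at q = 0.95, 12.2 at 0.90 and 2.5 at 0.80.

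Under either reading the definition as worded makes arm C's advantage look smaller than it would on starts. How much smaller cannot be fixed from the article.

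**Step 5. Direction.** Steps 3 and 4 both work against arm C. This holds if the outcome is restricted to participants with confirmed HCV and if arm C commencement really means drug begun. If it is recorded as drug handed over on site, the direction is less certain. Arm C also starts antibody-positive people before the RNA result, so counting RNA-negative starters would push arm C's uptake up.

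**The case against.** The strongest reply is that uptake is not arm C's test. Study outcomes explains: "The rationale for two primary outcomes is that arm C itself involves providing treatment to everyone found to have HCV as part of its intervention". The comparisons at issue are secondary or labelled subgroup analyses, and a bias against arm C is conservative. All of this stands and limits the weight of the point. It does not remove the three contrasts, which are still announced, or give them a common event.

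It can also be said that scoring diverted arm C participants is a detail for the analysis plan. That would hold if the article were silent. It states a rule instead, and the rule names study drug. No text says outright how such a participant is scored, so the misclassification is a consequence of the wording. The pregnancy route is narrow, because known pregnancy is already an exclusion.

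Three stronger readings are tempting, and the document does not support them:

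- **The primary results are biased.** They are not: both main uptake comparisons count scripts on each side, and arm C's main comparison is on cure. Study outcomes does word the cure outcome in terms of those who start treatment, but the Abstract gives it among all participants with HCV. The text does not establish that the uptake definition carries over.
- **The true C − B difference is 23.5 to 34 points.** Those figures need 70% to be a script rate, while Sample size speaks of participants expected to start treatment.
- **Arm C's uptake benefit is inflated.** The two mechanisms shown here point mostly the other way.

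**Conclusion.** The point holds for the contrasts of arm C with control, A and B on uptake: they compare different events, and the study-drug wording leaves out scripts that arm C participants obtain through standard of care. The likely effect is to understate arm C's advantage, subject to the two conditions on direction given above.

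The size is unknown. The 1.5 to 7.5 points for diverted participants rest wholly on assumed shares, and the script-to-start effect cannot be sized without a share that the article does not give. The weight is modest: a definition to correct before analysis, with no bearing on the three main comparisons.

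**What to change.** For the uptake contrasts involving arm C:

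1. Score commencement among RNA-confirmed participants in all arms, by any route and over the same window from enrolment, so that a script counts in arm C as it does elsewhere. A 12-week record review is already described for A and B.
2. Add a sensitivity analysis on confirmed treatment start wherever it is ascertained: the week 12 contact in A and B, study-drug start in C, and the record review in control.
3. State that a script and drug in hand are still not the same event, so that the arm C contrasts on uptake remain secondary.

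The main comparisons need no change. The cost is small, since medical record review is already a planned outcome source, but it is more than a wording change. The check for scripts must be extended to arm C, where no such review is described. Start data in control will be less complete, because that arm has only a record review at study close; the sensitivity analysis should be reported with that limit.

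### Primary outcome 2 (cure) has two conflicting denominators, and the version restricted to treatment starters conditions away much or all of the effect that arm C is meant to produce

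*Protocol article*

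**What the plan says.** The protocol article describes the cure outcome in five places.

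- **Abstract, Methods and analysis:** "the proportion of participants with HCV achieving cure". The denominator is everyone with HCV.
- **Introduction, last paragraph:** "We hypothesise that testing and same-day treatment will increase cure compared with standard clinical care". There is no condition on starting.
- **Study outcomes:** "The proportion of participants with HCV who start treatment achieving cure". The denominator is starters. Starting means receipt of a script in arms A, B and control, but commencement of study drug in arm C. The study nurse arranges a missing SVR visit in every arm except control.
- **Sample size:** the proportions "expected to achieve cure in each arm are 10% among controls, 30% in arm A, 50% in arm B and 70% in arm C". The denominator is given only as participants. Arm C versus control on cure is one of three comparisons, each tested at "a significance level of 0.05/3=0.0167".
- **Statistical analysis:** "All available binary outcomes will be analysed at the patient level", on an intention-to-treat basis defined by the cluster's randomised arm. The cure denominator is not stated. Best-worst and worst-best scenarios for missing SVR are sensitivity analyses.

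**The concern.** Cure is the only primary comparison for arm C. Study outcomes explains that a second primary outcome is needed because treatment provision is itself part of arm C. Arm C is therefore expected to raise cure mainly by getting more people started. A denominator of starters takes that step out. It compares the roughly 30% of controls who obtain a script with the roughly 90% in arm C who begin study drug, and these groups are selected by different processes after randomisation.

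The available-outcomes rule adds to this. Under the arm A follow-up section, which the other intervention arms adopt, SVR is looked up only for people who started. If only available SVR results are analysed, the comparison becomes cure among tested starters, which should lie near drug efficacy in any arm. Even the abstract's denominator would collapse to this unless non-starters are explicitly counted as not cured.

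If the text stays as it is, the denominator could be settled after results are seen, and the choice could decide whether arm C appears effective.

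**Working it through.** **Inputs.** From Sample size: proportions starting treatment of 30% (control), 50% (A), 70% (B) and 90% (C), and proportions cured of 10%, 30%, 50% and 70%. From the Introduction: direct-acting antiviral cure rates above 90%. Values of 90% and 95% are used below as assumptions for cure once treated and tested.

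**1. Which denominator do the planning rates fit?** Implied cure per starter = cure / start.

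| Arm | Start | Cure | Start minus cure | Cure / start |
|---|---|---|---|---|
| Control | 30% | 10% | 20 points | 33.3% |
| A | 50% | 30% | 20 points | 60.0% |
| B | 70% | 50% | 20 points | 71.4% |
| C | 90% | 70% | 20 points | 77.8% |

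Cure is the start rate minus 20 points in every arm, so the planned cure contrast for arm C (70 − 10 = 60 points) equals the start contrast (90 − 30 = 60 points). A 10% cure rate among control starters would be implausible beside cure rates above 90%. The rates therefore fit the unconditional denominator. This is an inference, because the section does not name the denominator.

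**2. The contrast on the plan's own rates.**

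- Per person with HCV: 70 − 10 = 60 points; OR = (0.70/0.30)/(0.10/0.90) = 21.
- Per starter: 77.8 − 33.3 = 44 points; OR = (0.778/0.222)/(0.333/0.667) = 7.

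**3. The contrast if cure per starter is the same in both arms.**

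- At 90%: difference per starter 0, OR 1. Per person with HCV: 0.30 × 0.90 = 27.0% vs 0.90 × 0.90 = 81.0%.
- At 95%: difference per starter 0, OR 1. Per person with HCV: 28.5% vs 85.5%.

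**4. Available SVR results only.** Suppose the planned cure rates count untested starters as not cured, and 90% of tested starters are cured. The share of starters tested is then 0.333/0.90 = 37% in control and 0.778/0.90 = 86% in arm C (35% and 82% at 95%). Restricting to tested starters gives 90% in both arms, a null result from the same data that give 10% vs 70%.

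**5. The planned missing-SVR scenarios, under the 90% assumption of step 4.**

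- Denominator starters. Best-worst: control 33.3%, arm C 0.778 + (1 − 0.864) = 91.4%. Worst-best: control 0.333 + (1 − 0.370) = 96.3%, arm C 77.8%. The direction changes.
- Denominator all with HCV, non-starters not cured. Best-worst: control 10%, arm C 0.90 × 0.914 = 82.2%. Worst-best: control 0.30 × 0.963 = 28.9%, arm C 70%. Both favour arm C.

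The scenarios therefore do not repair the starter denominator, but they do bound the missing-SVR problem once the denominator is everyone with HCV.

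**The case against.** Several points on the other side stand.

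- A reader might infer that the starter version would show arm C to be worse. The documents do not support this. On the plan's own rates it still favours arm C (33% vs 78%), provided untested starters count as not cured. Reversal needs lower cure per starter in arm C, for which no figure is given. With assumed rates of 95% and 85%, for example, the starter result is 10 points against arm C while cure per person with HCV is 28.5% vs 76.5%. This is a possibility only.
- A reader might infer that the planning rates cannot be per starter. That is too strong. The figure above 90% is efficacy once treated, and recorded cure per starter can be much lower when control participants are not recalled. As a rate per starter, 10% is implausible but 70% is not.
- It would be wrong to say that the plan abandons intention-to-treat. Its definition is analysis by the cluster's randomised arm, and the abstract's endpoint does not condition on starting.
- Participants in arm C told to discontinue after a negative RNA result are outside either denominator, because they do not have HCV. Only RNA-positive participants told to cease for renal impairment or hepatitis B coinfection remain among the starters.
- Treatment commencement is also compared between arm C and control, so the effect on starting will be visible. It is not arm C's primary comparison, however.
- The denominator of everyone with HCV is not perfect either. RNA-positive status is found through testing that differs by arm, and case finding is itself a secondary outcome.

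No loss of power is claimed for the starter version. That would need the RNA prevalence among recruits and the intracluster correlations, which the article does not give.

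None of these points settles which denominator is primary.

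**Conclusion.** The concern holds as a contradiction in the definition of a primary outcome, with consequences for what the arm C comparison can show. The article states two endpoints. The hypothesis supports the unconditional one, and so, by inference, do the planning rates. Followed as written, the Study outcomes version cuts the planned contrast from 60 to 44 points if untested starters count as not cured. It cuts it to nil if cure per starter is equal in the two arms or if only tested starters are analysed. The 60 and 44 points come from the plan's own rates; the nil result assumes a common cure rate among those treated and tested, with 90% or 95% used as illustrations. This should be corrected before the analysis is fixed.

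**What to change.** 1. Define outcome 2 once, in the same words, in the outcome, sample size and analysis sections: documented SVR among all enrolled participants with HCV (RNA-positive), analysed by the cluster's randomised arm, with non-starters counted as not cured.
2. Report cure among starters and cure among those tested as secondary outcomes.
3. State how starters without an SVR result count in the primary analysis. Counting them as not cured, with no SVR recall in control, would favour arm C. So either apply the same SVR ascertainment in all arms, or keep the best-worst and worst-best scenarios beside the primary result and state this limit.
4. Acknowledge that RNA-positive status is itself found through arm-dependent testing.

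**Cost.** Items 1, 2 and 4 are wording and need no new data, though the reported cure proportions will be lower in every arm than a rate per starter. Under item 3, equal ascertainment is a small change in conduct, in a trial that has been recruiting since March 2022. Keeping the scenarios and stating the limit costs only wording but leaves the uneven ascertainment in place.
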